## Results

The current study began in April 2025 and is currently in the preparatory phase. Previously, a preliminary pilot study was conducted in which 16 patients were recruited, of whom 9 received the VR intervention [16].

In this pilot study, using a distraction chosen by each participant, a significant reduction in pain (defined as a decrease of ≥2 points on the VAS compared to previous experience) was observed in 3 patients. Five patients reported no noticeable change (VAS difference of 0 or 1 points), and 1 patient experienced worsening symptoms and discontinued participation.

Additionally, anxiety, measured using the Goldberg Scale, decreased during the session in 4 patients, with “significant anxiety” defined as a score >2 points.

Regarding time perception, 50% of participants reported a notable difference in their perception of time passage 30 days after the intervention (considered significant if the treatment duration was perceived as 30 min).

These preliminary results provided the rationale for the current full-scale randomized controlled trial, which aims to evaluate whether the use of virtual reality is effective in reducing anxiety and chronic neuropathic pain. In the current protocol, a statistically significant reduction in heart rate and pain intensity in the intervention group compared to the control group will be considered a satisfactory outcome.

If the hypotheses are confirmed, this intervention could be implemented in routine care and extended to other procedures involving difficult-to-manage pain.

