**Objective:**

We aimed to evaluate the efficacy of VR in reducing pain and anxiety in patients with persistent neuropathic pain.

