**Methods:**

This randomized, controlled, multicenter, open-label trial involves two groups: an intervention group receiving VR sessions and a control group receiving standard pharmacological treatment. Participants are adults aged 30‐61 years diagnosed with neuropathic pain, unresponsive to flexible doses of gabapentin. Pain and anxiety levels are assessed using the Pain Detect Questionnaire, Visual Analog Scale (VAS), and Goldberg Anxiety Scale at baseline and follow-up points. VR sessions are conducted weekly for 3 weeks, each lasting 30‐35 minutes. Perceived time during VR sessions is recorded as an indirect measure of distraction effectiveness. The primary outcome is the reduction in pain intensity and anxiety levels post-intervention compared to baseline. A sample size of 30 patients (15 per group) was calculated to achieve 80% statistical power, considering a 2-point mean difference in VAS scores.

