#### Data Collection, Information Sources, and Intervention

Data collection will begin once the patient has provided written informed consent. Patient assignment to a study group will be randomized using the RandomizedR computer system.

The data collector will record the patients’ age, sex, study group, and type of intervention performed. Before contacting the patient with the virtual reality device, the patient’s status and heart rate will be recorded upon arrival at the clinic, regardless of the assigned study group.

Patients in Group 1 will be the intervention group. They will undergo 10 virtual reality pain treatment sessions (Monday to Friday for 2 weeks), with each session lasting 30 minutes, while maintaining treatment with gabapentin at a dose of 1200 mg/24 h. Their clinical history, pain situation, and anxiety will be assessed in each session.

Patients in Group 2 will be the control group. Their clinical history, pain situation, and anxiety will be assessed in each session. They will receive pain treatment with oral gabapentin at a dose of 1200 mg/24 h. The control group will receive standard care without any VR exposure. Participants will remain in a quiet room with standard analgesic treatment as prescribed. No additional relaxation stimuli will be provided. Outcome data will be collected in parallel with the intervention group.

Figure 2 shows the CONSORT diagram.

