## Discussion

### Principal Findings

This protocol outlines a randomized controlled trial aimed at evaluating the impact of VR on reducing anxiety and chronic neuropathic pain. Based on a previous pilot study and literature supporting the use of immersive distraction therapies [6,8,10], we hypothesize that VR will significantly improve patient-reported outcomes in terms of pain perception, anxiety levels, and treatment satisfaction.

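### The stated success criterion (heart rate and pain) does not match the stated primary outcome (pain and anxiety), and the only heart-rate reading described precedes contact with the VR device

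*Protocol article*

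**What the plan says.** The success statement stands in the Results section, in a sentence about the current protocol and not the pilot. What it counts as satisfactory is "a statistically significant reduction in heart rate and pain intensity in the intervention group compared to the control group". It is the only success criterion in the article.

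The Methods paragraph of the abstract sets a different target: "The primary outcome is the reduction in pain intensity and anxiety levels post-intervention compared to baseline". The objective in the abstract reads "We aimed to evaluate the efficacy of VR in reducing pain and anxiety in patients with persistent neuropathic pain". The sentence just before the success statement describes the trial as one "which aims to evaluate whether the use of virtual reality is effective in reducing anxiety and chronic neuropathic pain". The Principal Findings section hypothesises that "VR will significantly improve patient-reported outcomes in terms of pain perception, anxiety levels, and treatment satisfaction".

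Heart-rate collection is described once, under Data Collection, Information Sources, and Intervention (in the recruitment part). The reading is timed "Before contacting the patient with the virtual reality device", and "heart rate will be recorded upon arrival at the clinic, regardless of the assigned study group". The per-session assessments in the same section cover clinical history, pain and anxiety. The Data Analysis section includes heart rate among the comparisons between groups but gives no time point. The Statistical Analysis section lists pain, anxiety and satisfaction for the two-tailed t test, without heart rate.

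**The concern.** A trial needs one definition of success, fixed in advance. This article has two, and they differ in the variables (heart rate in place of anxiety) and in the contrast (between groups in place of change from baseline). Which sentence is followed can change the trial's conclusion.

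Heart rate is also an awkward variable to decide on here. It does not appear in the objective, the hypothesis, the t-test list or either sample-size statement, and the only reading described comes before the patient meets the device. A reading at that point cannot show an effect of that day's session.

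The trial is open-label and its main outcomes are self-reported. If the definition of success is left ambiguous, it can be settled after the results are known, and the nominal 5% level then no longer describes the chance of a false claim.

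**Working it through.** The plan gives no figure for this point, so the check is mainly a comparison of statements.

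**Variables named in each place**

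| Place in the article | Pain | Anxiety | Heart rate | Satisfaction |
|---|---|---|---|---|
| Abstract, Objective | yes | yes | no | no |
| Abstract, Methods (primary outcome) | yes | yes | no | no |
| Results, aim | yes | yes | no | no |
| Results, success statement | yes | **no** | **yes** | no |
| Principal Findings, hypothesis | yes | yes | no | yes |
| Data Analysis, group comparison | yes | yes | yes | no |
| Statistical Analysis, t test | yes | yes | no | yes |

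The success statement is the only row without anxiety. Heart rate appears in one other row, which gives no time point.

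**Contrast.** The primary outcome is worded as post-intervention against baseline. The success statement is worded as intervention against control. Only the second uses the randomised comparison.

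**What follows from the mismatch**

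1. Pain and heart rate fall, anxiety does not change: the success statement is met, but half of the primary outcome shows nothing.
2. Pain and anxiety improve, heart rate does not change: both parts of the primary outcome are met, but the stated criterion is not.

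**Size of the second case, as a bound.** Assume that both heart rate and pain must be significant in favour of VR, and that arrival heart rate is unaffected by VR. A two-sided 5% test favours VR by chance with probability 0.05 / 2 = 0.025. The probability that two events both occur cannot exceed that of either one, so the criterion is met at most 2.5% of the time, whatever the pain effect and the correlation.

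**Illustration with the Sample Size section's own inputs** (1-point difference, SD 3, 25 per group, two-sided 5%):

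- Standard error = 3 × √(2/25) = 0.849
- Power for pain = Φ(1/0.849 − 1.96) = Φ(−0.78) ≈ 0.22
- Joint probability under independence = 0.217 × 0.025 = 0.005; with an assumed correlation of 0.5 it is 0.017

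So the range is about 0.5% to 1.7%, conditional on the same two assumptions.

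**Pain instrument.** The section on data collection and sources of information assigns pain intensity to both PainDETECT and VAS. The abstract's sample size is based on a VAS difference, and the only clinically significant pain change defined is on that scale. VAS is therefore the natural deciding instrument, although no sentence says so.

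**The case against.** The success sentence is narrative text, and it says that such a result would be satisfactory. That is a sufficient condition. A reader might infer that the trial must fail if heart rate does not fall, but the article does not say this. It is why the second case above is described as missing the stated criterion, and why the 2.5% bound depends on reading the rule as requiring both parts.

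A reader might also infer that no heart rate is taken after VR. The article supports only the weaker statement that none is described. Heart rate is listed as a group comparison, the timeline figure is not available here, and a full measurement schedule may stand in the full protocol. If the arrival reading is repeated at each visit, later readings would follow earlier sessions and could show a cumulative effect. The article does not say whether it is repeated.

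A third tempting inference is an inflated false-positive rate. Four independent 5% tests would give 1 − 0.95⁴ = 18.5%, but only under a rule that any one of four outcomes may count. No section states such a rule, and independence is itself an assumption.

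Finally, the Masking section says that the person responsible for the data analysis will not take part in the intervention. That limits one source of bias, but an analyst would still have two definitions of success to choose from.

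None of this removes the contradiction between the abstract and the Results section.

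**Conclusion.** The contradiction stands and should be corrected before any outcome data are examined. The success statement and the primary outcome share only pain, and every statement of purpose in the article sides with pain and anxiety. This rests on the text alone and needs no numerical assumption.

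The heart-rate timing point stands in a limited form: the only reading described is before device contact, and the time point of the planned comparison is not given. Whether other readings are planned cannot be settled from this article.

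The consequence is a possible reversal of the trial's conclusion in either direction. The 2.5% ceiling holds only if both parts are required and arrival heart rate is unaffected by VR; the 0.5% to 1.7% range is an illustration and not a forecast.

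**What to change.** 1. Rewrite the success sentence in the Results section to match the primary outcome: a between-group comparison, VR against control, of pain on VAS and of Goldberg anxiety at one fixed post-treatment time. Reword the abstract's primary outcome to the same contrast and time.
2. State how the two outcomes combine. Either both must be significant at 5%, or they are tested in fixed order, VAS first and anxiety only if VAS is significant. Either choice holds the 5% level.
3. Make heart rate and PainDETECT secondary, and align the Data Analysis and Statistical Analysis sections with that.
4. Give the time point for heart rate. Interpret it as a treatment effect only if it is read after VR exposure, and at the matching time in the control arm.

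The cost of steps 1 to 3 is protocol wording, and the article describes the trial as still in its preparatory phase. The small downside is that heart rate no longer counts towards success.

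The choice in step 2 has its own price. Requiring both outcomes lowers power: two tests with 80% power each succeed together with probability 0.8 × 0.8 = 64% under independence, or about 69% at an assumed correlation of 0.5. The fixed order avoids that loss for VAS, but a claim on pain can then be made without an anxiety effect, so the sentence should say plainly what each result would mean. If step 4 leads to a post-session heart rate, that is one more measurement in both arms.

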## Discussion

### Principal Findings

This protocol outlines a randomized controlled trial aimed at evaluating the impact of VR on reducing anxiety and chronic neuropathic pain. Based on a previous pilot study and literature supporting the use of immersive distraction therapies [6,8,10], we hypothesize that VR will significantly improve patient-reported outcomes in terms of pain perception, anxiety levels, and treatment satisfaction.

### Comparison With Prior Work

Several previous studies have demonstrated the analgesic and anxiolytic effects of VR in clinical contexts such as dental procedures, burn care, and pediatric interventions [7,8,17-19]. However, there is a scarcity of research targeting adults with pharmacoresistant neuropathic pain, a population with limited treatment options [20]. Our protocol addresses this gap and builds upon evidence showing that immersive experiences can activate cortical regions involved in pain modulation [12].

### Strengths and Limitations

A strength of this study is the integration of immersive VR with standard pharmacologic therapy in a structured and replicable design. Limitations include the lack of home-use devices, potential biases in self-reported outcomes, and the absence of personalization in VR content. Additionally, the exclusion of older adults limits generalizability.

### Future Directions and Dissemination

Future studies should explore the feasibility of home-based VR systems and allow patients to select content tailored to their preferences to maximize engagement. Results of this study will be disseminated through peer-reviewed journals, clinical conferences, and institutional briefings, supporting broader implementation in pain management strategies.

### Conclusion

If the expected outcomes are confirmed, VR could represent a scalable, non-pharmacological adjunct for managing chronic pain and anxiety, potentially transforming routine clinical practices.
